#### Quality of life

Quality of life will be measured using the EQ-5D, SF-12, and Satisfaction with Life Scale. The EQ-5D and SF-12 will be assessed at baseline and at the 6-month assessment, while the Satisfaction with Life Scale will be administered at baseline, 3 months, and 6 months. The EQ-5D is a questionnaire consisting of five dimensions and a Visual Analog Scale (VAS) that allows individuals to rate their perceived health status on a scale from 0 to 100 [74]. The SF-12 is a questionnaire comprising 12 questions designed to evaluate both the physical and mental health of individuals. It has been validated for use within the Chinese population [75]. Satisfactory of life scale of participants will be assessed by a single item ranging from 0 to 10, with higher scores indicating greater life satisfaction.

#### Factors for exploratory analysis

Social media addiction will be measured with the Bergen Social Media Addiction Scale (BSMAS) at baseline and at the 6-month assessment. The BSMAS is a 6-item self-reported scale with a total score ranging from 6 to 30. A higher score reflects higher social media addiction [76].

The 8-item eHealth Literacy Scale will be used to measure participant’s perceived skill to use information technology for health-related reasons at baseline and at the 6-month assessment [77].

Body composition will be measured with the Tanita RD545 body composition scale at baseline and at the 6-month assessment (Tanita Corp., Japan). The skeletal muscle mass measured by this machine was validated against Lunar iDXA (GE HealthCare Technologies Inc., USA) in older adults [78]. Information on body fat, muscle mass, and body water will be collected.

Pulse wave velocity (PWV) will be measured with the SMT Medical-Vicorder (80 beats medical, Germany) at baseline and at the 6-month assessment. The Vicorder machine is a non-invasive measurement of vascular health and has demonstrated sufficient accuracy and validity in measuring PWV when compared to the SphygmoCor machine (Cardiex Ltd, Australia), which is a validated non-invasive PWV measurement machine [79, 80]. Participants who took part in the project in the Sha Tin, N.T. study site, will have access to PWV measurement, and it will be conducted within the same district. A total of 167 participants will be invited for PWV measurements.

The Huawei Watch Fit 2 will be provided to participants in arm 1 and arm 3. The watch will collect parameters including HR and daily step count. Step count data will be averaged weekly and presented as mean ± SD. HR data will be used to identify periods of physical activity and to determine whether participants have reached specific HR zones associated with physical activity. As only participants in arm 1 and arm 3 will receive the HW, data will be compared within each arm and between arms 1 and 3 for the periods of 0–3 months and 3–6 months.

The Life's Essential 8 (LE8) composite score at baseline and at 6-month assessment will be calculated using lifestyle and biometric data such as diet, physical activity, sleep duration, smoking status, BMI, BP, FBG, and blood lipid levels. The LE8 score ranges from 0 to 100, with higher scores reflecting a healthier lifestyle and better cardiovascular health [81]. This score is based on the latest guidelines from the AHA for cardiovascular health. Our study was planned before LE8 became available. Therefore, it is included as an exploratory variable.

For continuous secondary outcome measurements—including biometric data (FBG, TC, LDL, HDL, TG, SBP, DBP, and QRISK3 score), lifestyle parameters (AUDIT-C score, physical activity parameters, MD score, PSQI score), mental parameters (PSS-10 score, GAD-7 score, PHQ-9 score, 6-item De Jong Gierveld Loneliness Scale, 10-item General Self Efficacy Scale), quality of life (SF-12, EQ-5D, satisfaction of life scale), and exploratory parameters (BSMAS, 8-item eHealth Literacy score, body composition data, Huawei Watch Fit 2-related parameters, LE8 score), the 6-month and, if available, 3-month assessment data will be compared with baseline values. Data will be presented as mean ± SD. For categorical secondary outcomes, the distribution of each outcome at every assessment time point will be analyzed and compared to baseline. Descriptive statistics (such as counts and percentages) will be presented for each category.

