### Secondary outcomes

#### Biometric data

All biometric data, including SBP, DBP, and biochemical markers (FBG, TC, LDL, high-density lipoprotein (HDL), and TG), were collected at baseline and at the 6-month assessment time point. All parameters will be analyzed and presented as mean ± SD. Analyses will compare the differences between baseline and 6-month values. In addition, all biometric data will be further categorized based on its clinically significant thresholds [47–50].

SBP and DBP are measured by a validated automated office BP (AOBP) device (Microlife WatchBP Office 2G, Microlife Corp., Taiwan). The BP measurement procedures follow the standards of 2021 European Society of Hypertension practice guidelines for office BP measurement [47]. The BP device automatically takes three BP readings within a 1-min interval and provides a mean BP value for analysis, in the absence of healthcare workers to prevent white-coat effects. The device also does not display BP numbers during the 3-min measurement period.

In addition, the 10-year risk of developing CVD of participants at baseline and at the 6-month assessment timepoint will be estimated by QRISK3 score, using participants’ BP, blood cholesterols, BMI, and medical history. QRISK3 estimates an individual’s risk of developing CVD within the next 10 years [51].

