Smoking status of the participants was assessed by categorizing individuals as current smokers (1–10 cigarettes per day, 11–20 cigarettes per day, or more > 20 cigarettes per day), past smokers (having quit smoking within the past 12 months or more than 12 months ago), or non-smokers at baseline, at 3-month, and at the 6-month assessment. The distribution of smoking status at each assessment will be analyzed and compared with that at baseline.

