## Statistical analysis

To address the primary objective, the global comparison test, we will first conduct ANCOVA analysis, using baseline primary outcomes measures (LS7 score) as the covariates and the 6-month measurement as the outcome. For objective 2, we will conduct the same statistical analysis to compare arm 1 (HC + HW) vs arm 4 (waiting group). Similar analyses will be conducted for the other objectives. We will use Bonferroni correction to control the family-wise type I error rate at 0.05.

For exploratory analyses, we will conduct similar analytical plan for the secondary outcomes and subgroup analyses to investigate baseline influence. Post hoc tests will be used to investigate which pairs of levels within a factor differ after an overall (main effect) difference has been established.

We will use linear mixed models (LMMs) to address missing data. LMMs use likelihood-based estimation and are robust in addressing various types of missing data, including missing at random (MAR). Unlike imputation methods, LMMs leverage all information available in the current data, including fixed and random effects which minimizes potential biases related to imputation [82].

Statistical analysis will be performed in R, which is a free-of-charge computer software. Both intention-to-treat (ITT) and per-protocol approach will be used when comparing results across the 4 arms. For the ITT analysis, all randomized participants will be included. For the per-protocol analysis, only participants who have completed all assessments will be included.

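### For categorical secondary outcomes the specific text names a comparison with baseline, which cannot show an intervention effect, and the Statistical analysis section does not supply a between-arm model that fits categories

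*Protocol article*

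**What the plan says.** The Lifestyle behavior section says of smoking: "The distribution of smoking status at each assessment will be analyzed and compared with that at baseline". The closing paragraph of Factors for exploratory analysis gives the general rule for categorical secondary outcomes: "the distribution of each outcome at every assessment time point will be analyzed and compared to baseline". It continues: "Descriptive statistics (such as counts and percentages) will be presented for each category". The Biometric data section adds that biometric measures will also be categorised at clinical thresholds, and Lifestyle behavior says that activity will be categorised by WHO standards, so the rule reaches those outcomes too.

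Continuous secondary outcomes are worded in the same way. Biometric data has "Analyses will compare the differences between baseline and 6-month values", and the closing paragraph has "the 6-month and, if available, 3-month assessment data will be compared with baseline values".

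The Statistical analysis section says: "we will conduct similar analytical plan for the secondary outcomes and subgroup analyses to investigate baseline influence". The plan it points back to is ANCOVA, "using baseline primary outcomes measures (LS7 score) as the covariates and the 6-month measurement as the outcome", with linear mixed models for missing data. The section also mentions post hoc pairwise tests, and intention-to-treat and per-protocol analyses for comparing the four arms.

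**The concern.** The abstract makes the impact on secondary outcomes, and comparison between intervention groups, secondary objectives. A comparison of follow-up with baseline answers neither. It mixes any intervention effect with everything else that changes over six months: regression to the mean after selection, the baseline risk assessment session that every arm receives, and the passage of time. The waitlist arm exists to remove these influences, and a contrast with baseline does not use it.

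If the specific sentences were followed as written, a shift in smoking or activity categories within an intervention arm could be reported as benefit although the waitlist arm had shifted as much. The Discussion section itself faults an earlier prevention programme for lacking a control group; a baseline-only comparison has the same weakness.

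**Working it through.** The protocol gives no figure for this point. Its disjunctive power of 0.901 concerns the primary outcome. It reproduces at 0.9005 with 180 per arm and a one-sided level of 0.05/3, and has no bearing here.

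**1. The sections side by side**

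- Smoking (Lifestyle behavior): contrast with baseline; no model; no arm contrast.
- Categorical secondary outcomes (Factors for exploratory analysis): contrast with baseline; counts and percentages; no arm contrast.
- Secondary outcomes in general (Statistical analysis): a plan similar to the primary one, hence between arms; the named models are ANCOVA and linear mixed models.

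For continuous outcomes the last item supplies a usable between-arm analysis. For categories it signals the intent, but the named models do not apply as written. The only stated analysis that can be applied directly to a category is the one against baseline.

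**2. Drift without an intervention effect**

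*Selected on risk.* Entry requires at least two of seven items, among them low activity, poor diet and BMI of 23 kg/m² or more. Take a standard normal measure with baseline to 6-month correlation r (assumed 0.6 to 0.9) and people selected above the mean. The share still above it at follow-up is 1/2 + arcsin(r)/π:

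- r = 0.6: 0.5 + 0.6435/3.1416 = 0.705
- r = 0.9: 0.5 + 1.1198/3.1416 = 0.856

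The adverse share falls from 100% to between 71% and 86%, an apparent improvement. This applies to people who enter through that item, not to the whole sample.

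*Capped by exclusion.* SBP of 135 mmHg or more, DBP of 85 mmHg or more, high lipids and QRISK-3 of 15% or more are excluded. A category starting at such a cut is empty at baseline and can only fill. With people selected below +1 SD (assumed), the share above the cut rises from 0% to 10.3% at r = 0.6 and to 5.1% at r = 0.9, an apparent worsening. Total cholesterol is subject to both: it is an entry item from 6.2 up to 8 mmol/L and an exclusion from 8 mmol/L.

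*Elapsed time.* Past smokers are split at 12 months since quitting. Someone who quit more than 6 and up to 12 months before baseline and stays abstinent is past 12 months at the 6-month assessment, in any arm.

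**3. Size, over a range of assumed rates**

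Assume no intervention effect, 180 analysed per arm (720/4), 60% adverse at baseline (108 adverse, 72 not) and 8% of the 72 worsening (5.76 expected). For a within-arm McNemar test, z = (improved − worsened)/√(improved + worsened). At the expected counts:

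| Adverse group improving | Improved | z | Within-arm p < 0.05 (simulated) | Two-arm p < 0.05 (simulated) |
|---|---|---|---|---|
| 10% | 10.8 | 5.04/√16.56 = 1.24 | 23.4% | 5.0% |
| 20% | 21.6 | 15.84/√27.36 = 3.03 | 89.4% | 5.2% |
| 30% | 32.4 | 26.64/√38.16 = 4.31 | 99.7% | 5.1% |

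The last two columns come from 20,000 simulated pairs of arms per row. The chance that all four arms are significant together is 0.234⁴ = 0.3%, 0.894⁴ = 64% and 0.997⁴ = 99%.

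**The case against.** The strongest reply is that wording about baseline in this article's outcome sections describes how an outcome is expressed, not the inferential contrast. The primary outcome is introduced in the same way, as the LS7 score at 6 months against baseline, and is then analysed between arms by ANCOVA. The Statistical analysis section extends that plan to secondary outcomes and speaks of comparing the four arms. Where the authors mean a within-arm comparison, as for the watch data, they say so. The choice of regression for a category is also commonly left to an analysis plan, which is not shown.

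Much of this stands, and it rules out three stronger readings that a reader might infer:

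- *That only comparisons with baseline are planned.* The Statistical analysis section contradicts this.
- *That within-arm significance tests are planned.* None is named, and the text following the categorical rule refers to descriptive statistics. The McNemar test above shows what would happen if the stated contrast were tested.
- *That every arm will appear to improve.* This does not hold for BP, lipids or QRISK-3, where capping at entry pushes the other way. Even for improving items it depends on the assumed rates.

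The absence of a categorical model would not be a finding by itself. What remains is that the article does state a contrast for these outcomes, and it is not the randomised one. The parallel with the primary outcome is incomplete: there the Statistical analysis section supplies a model that fits, so the baseline wording does no harm. The watch-data sentence also cuts both ways, because it shows that the authors name a between-arm contrast when they intend one.

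**Conclusion.** The point holds in a limited form. For categorical secondary outcomes the specific sentences name a contrast that cannot show an intervention effect. The general sentence implies the right contrast, but with models that do not fit. The two need to be reconciled in favour of the randomised comparison.

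The consequence is confined to secondary outcomes. The possible size of misleading change depends on assumed transition rates and correlations, since the article gives none: from 23% to nearly 100% of arms in the illustration, against about 5% for a two-arm test. The direction differs by outcome. The conclusion does not rest on any one of these rates, only on the fact that change from baseline can occur without an intervention effect. For continuous secondary outcomes there is only an inconsistency of wording, because ANCOVA already fits them.

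**What to change.** In Lifestyle behavior (smoking) and in the closing paragraph of Factors for exploratory analysis, state that the inferential comparison for categorical secondary outcomes is each intervention arm against waitlist at follow-up. Use logistic regression for two categories or proportional-odds regression for ordered ones, adjusted for baseline category, and report an odds ratio with its interval. State that within-arm change from baseline is descriptive and carries no test.

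For continuous secondary outcomes, only align the wording in Biometric data and in the closing paragraph with the ANCOVA already stated in Statistical analysis.

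The cost is a few sentences and a standard regression on data already being collected. No visit, measurement, sample-size or power figure changes. The wording should be settled while the analysing statisticians are still blinded to allocation.

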## Statistical analysis

To address the primary objective, the global comparison test, we will first conduct ANCOVA analysis, using baseline primary outcomes measures (LS7 score) as the covariates and the 6-month measurement as the outcome. For objective 2, we will conduct the same statistical analysis to compare arm 1 (HC + HW) vs arm 4 (waiting group). Similar analyses will be conducted for the other objectives. We will use Bonferroni correction to control the family-wise type I error rate at 0.05.

For exploratory analyses, we will conduct similar analytical plan for the secondary outcomes and subgroup analyses to investigate baseline influence. Post hoc tests will be used to investigate which pairs of levels within a factor differ after an overall (main effect) difference has been established.

We will use linear mixed models (LMMs) to address missing data. LMMs use likelihood-based estimation and are robust in addressing various types of missing data, including missing at random (MAR). Unlike imputation methods, LMMs leverage all information available in the current data, including fixed and random effects which minimizes potential biases related to imputation [82].

Statistical analysis will be performed in R, which is a free-of-charge computer software. Both intention-to-treat (ITT) and per-protocol approach will be used when comparing results across the 4 arms. For the ITT analysis, all randomized participants will be included. For the per-protocol analysis, only participants who have completed all assessments will be included.

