**Methods:**

This 4-arm randomized controlled trial (RCT) aims to recruit 1000 middle-aged individuals without chronic diseases into four arms: health coaching (HC), health watch (HW), a combination of both (HC + HW), or waitlist control. The primary objectives are to assess the effectiveness of HC + HW compared to the waitlist group, as well as the effectiveness of HC-only and HW-only interventions. Secondary objectives include evaluating the impact on secondary outcomes and comparing the effectiveness between intervention groups. Life's Simple 7 (LS7) composite score will be assessed, along with biometric parameters and a risk assessment survey. Participants will undergo evaluations at 0 month, 3 months, and 6 months after randomization.

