## Objective and hypothesis

Participants will be randomized to one of the following arms: HC, HW, both interventions combined (HC + HW), or waitlist control. The primary objectives of this RCT is to investigate the effectiveness of each of the three intervention arms (HC + HW, HC, HW) in improving Life's Simple 7 (LS7) composite score (an integrated lifestyle score that assesses seven health metrics for cardiovascular health as defined by the American Heart Association (AHA)) [32], compared with waitlist control. Comparisons of effectiveness between the interventional arms (HC + HW, HC, HW) will be our secondary outcomes. We hypothesize that HC and HW, individually or in combination, will improve participants’ lifestyle behaviors, resulting in a higher LS7 score, when compared with waitlist control. We further hypothesize that combining HC and HW will result in superior effectiveness than either component alone.

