### Sample size calculation

We used a web-based multi-arm clinical trial sample size calculator [35] for the sample size (or power) calculation. In this four-arm trial, with three experimental treatments and a waitlist arm, the hypotheses to be tested will be:$${H}_{k}:{\tau }_{k}={\mu }_{k}-{\mu }_{0}\le 0,\hspace{0.25em}k=1,\dots ,3.$$

The *global null hypothesis*, $${H}_{G}$$, will be:$${\tau }_{1}={\tau }_{2}={\tau }_{3}=0.$$

The *global alternative hypothesis*, $${H}_{A}$$, will be:$${\tau }_{1}={\tau }_{2}={\tau }_{3}={\delta }_{1}.$$

The *least favorable configuration* for experimental arm $$k$$, $$LF{C}_{k}$$, will be:$${\tau }_{k}={\delta }_{1},\hspace{0.25em}{\tau }_{1}=\cdots ={\tau }_{k-1}={\tau }_{k+1}=\cdots ={\tau }_{K}={\delta }_{0}.$$

Here, *δ*_1_ represents the interesting treatment effect, which was defined as LS7-score difference of 0.44 with a common standard deviation (SD) of 1.57, and *δ*_0_ represents uninteresting treatment effects, which was defined as the smallest mean difference between the intervention and control arm that would make the intervention clinically significant, and was set to be 0 [35]. Due to a lack of evidence, we will not explicitly test the interaction effect of HC and HW. The combined intervention will be analyzed as a distinct arm compared to the control, rather than a factorial combination. Under the global alternative hypothesis, a sample size of (*N* = 720) will have a disjunctive power (power to reject at least one null hypothesis) of 0.901 after Bonferroni’s correction. This estimation used a balanced target group allocation and a 0.05 significance level. The assumed mean and SD were based on our ongoing cohort study of 1862 participants who received HC + HW interventions. The participants in this cohort study have the same eligibility criteria as those in the proposed trial. According to previous studies, an improved LS7 score of 0.44 is considered a significant health improvement [36–38]. We propose a target sample size of 1000, allowing for a dropout rate of up to 28%. However, the observed dropout rate in the cohort study is much lower (3.8%).

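### The Statistical analysis section names a global test as the primary objective, which contradicts the three waitlist comparisons that the Objectives define as primary and on which the trial was sized

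*Protocol article*

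**What the plan says.** Four places in the protocol article bear on which hypothesis is primary.

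- **Abstract, Methods:** "The primary objectives are to assess the effectiveness of HC + HW compared to the waitlist group", together with HC alone and HW alone. Comparisons between interventions are secondary.
- **Objective and hypothesis:** the primary aim is to "investigate the effectiveness of each of the three intervention arms (HC + HW, HC, HW", each against waitlist, on the LS7 score. Comparisons between the active arms are again secondary.
- **Sample size calculation:** three hypotheses, one per active arm, each of the one-sided form that the arm's mean difference from waitlist is at most zero. The assumed effect is an "LS7-score difference of 0.44 with a common standard deviation (SD) of 1.57". At N = 720 the design "will have a disjunctive power (power to reject at least one null hypothesis) of 0.901" after Bonferroni correction, when all three effects equal 0.44.
- **Statistical analysis:** "To address the primary objective, the global comparison test, we will first conduct ANCOVA analysis". Next comes "For objective 2, we will conduct the same statistical analysis to compare arm 1 (HC + HW) vs arm 4 (waiting group", then similar analyses for the remaining objectives, then "We will use Bonferroni correction to control the family-wise type I error rate at 0.05". The family of tests to be corrected is not named.

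The article contains no numbered list of objectives to which the label of a second objective could refer.

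**The concern.** The first three places agree with one another, and the fourth does not. It names a different primary test and places the headline comparison, HC + HW against waitlist, after it.

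This matters because the two tests answer different questions. A global test of four means asks whether the arms differ at all. A significant result does not say which arm beats waitlist. It can also come from a difference between two active arms, a question the Objectives make secondary. Followed literally, the plan could give a positive primary result with no arm shown better than waitlist, or a negative one while HC + HW passes its own corrected test. The power of 0.901 was also calculated for a different test from the one now called primary.

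**Working it through.** **Inputs**, all from the Sample size calculation: effect 0.44; SD 1.57; N = 720 in four equal arms, so n = 180 per arm; family-wise level 0.05; Bonferroni over three one-sided hypotheses.

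**1. The plan's own figure.** The standard error of a contrast is 1.57 × √(2/180) = 0.1655, so each Z has mean 0.44/0.1655 = 2.659. The contrasts share the control arm, so their pairwise correlation is 0.5. The one-sided critical value at 0.05/3 is 2.128. Then 1 − P(all three Z ≤ 2.128) = 0.9005, which reproduces the stated 0.901. The power of any single contrast is Φ(2.659 − 2.128) = 0.702.

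**2. The same contrasts two-sided.** The critical value is 2.394. Power for at least one contrast is 0.836, and for a single contrast 0.604. The stated figure is therefore the one-sided one.

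**3. Omnibus F-test, all effects 0.44.** The arm means are (0.44, 0.44, 0.44, 0), with mean 0.33. The sum of squared deviations is 3 × 0.11² + 0.33² = 0.1452. Non-centrality is 180 × 0.1452 / 1.57² = 10.60. With 3 and 716 degrees of freedom at 0.05, power is **0.785**. Reaching 0.901 would take 243 per arm (N = 972).

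**4. Splitting the gap.** The total is 0.901 − 0.785 = 0.116. Sidedness accounts for 0.901 − 0.836 = 0.065, because the F-test has no direction. The remaining 0.836 − 0.785 = 0.051 is due to the change of test.

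**5. Sensitivity.**

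| Case | Omnibus F | At least one one-sided Bonferroni contrast |
|---|---|---|
| All effects 0.44, n = 180 | 0.785 | 0.901 |
| Only one arm works (0.44, 0, 0), n = 180 | 0.785 | 0.703 |
| All effects 0.44, 3.8% dropout (250 × 0.962 = 240.5 per arm) | 0.899 | 0.961 |
| All effects 0.44, no dropout (n = 250) | 0.911 | 0.967 |

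The F-test has the same power in the first two rows because the squared deviations are equal: 0.33² + 3 × 0.11² = 0.1452.

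**6. Baseline covariate.** The article does not say whether 1.57 is an unadjusted or an adjusted SD, and it gives no baseline correlation. If 1.57 is unadjusted, the non-centrality is divided by 1 − ρ². F-test power at n = 180 is then 0.826, 0.898 or 0.941 for an assumed ρ of 0.3, 0.5 or 0.6. The contrasts would gain as well. Neither 0.785 nor 0.901 includes this gain, so the two are on the same footing.

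**7. If the F-test were a gate.** In simulation with all effects 0.44 and n = 180, the F-test and at least one one-sided contrast are both significant with probability 0.784, against 0.900 ungated. In about 0.900 − 0.784 = 0.116 of such trials, a contrast would pass while the global test would not.

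**The case against.** The strongest reply is that this is a matter of labels. Every primary comparison in the Objectives is still analysed by the same ANCOVA, with family-wise error controlled. The article never calls HC + HW versus waitlist secondary, and its label may come from a numbered list in the full protocol. The Sample size calculation also defines a global null hypothesis. If the global comparison means rejecting that null through any of the three Bonferroni tests, 0.901 is the right power.

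Part of this stands. The figure of 0.785 does depend on the omnibus reading. That reading is the natural one, because the global test is run first by ANCOVA and listed separately from arm 1 versus arm 4. The label may be a leftover, but the article still states a primary test that conflicts with its own objectives and sizing.

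A reader might infer several stronger things that the article does not support:

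- **That the global test can block a finding for HC + HW.** The primary paragraph gives an order of analysis, not a condition. The only conditional wording, on post hoc tests after an overall difference, stands in the exploratory paragraph.
- **That the trial is simply less powerful than stated.** The 0.901 is calculated correctly for its own test. The F-test is the stronger of the two if only one arm works, and N = 720 is the floor at 28% dropout.
- **That the Bonferroni divisor could be as large as 6.** The family is not named beside the correction, but the sizing uses three hypotheses and the Objectives place between-intervention comparisons outside the primary set. The documents point to 3.
- **That Bonferroni is an error.** It is valid and matches the sizing; a stepwise method is only more efficient.

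**Conclusion.** The contradiction is plain in the text and has to be resolved, because it determines which result decides the trial. The global test named as primary cannot identify an effective arm and is not the test that was sized.

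The power difference is secondary and conditional. It is 0.785 against 0.901 (0.836 two-sided), assuming an omnibus F-test, all three effects at 0.44, SD 1.57 with no covariate gain, and 28% dropout. It reverses if only one arm works (0.785 against 0.703). At the cohort's 3.8% dropout the F-test itself reaches about 0.90 with all effects equal. A fall from 0.90 to about 0.78 through gating would arise only if a gate were added, and none is stated.

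**What to change.** Rewrite the first paragraph of the Statistical analysis section as follows.

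- The primary analysis is one ANCOVA of the 6-month LS7 score on arm and baseline LS7, with three contrasts: HC + HW, HC and HW, each against waitlist.
- These three contrasts are the sole primary family, with family-wise error 0.05, divisor 3 and the same sidedness as the Sample size calculation.
- They are tested whatever the global test shows. The omnibus F-test is reported descriptively.
- Contrasts between interventions stay secondary and outside this family, as the Objectives already say.
- The reference to a second objective is removed or tied to a stated list.

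The cost is wording and a few lines of R, with no new data. The change should be dated before any comparison between groups is seen.

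Optionally, Holm's procedure could replace single-step Bonferroni. It controls the same error rate, and two-sided power per arm rises from 0.60 to about 0.68 when all effects are 0.44. Its confidence intervals are less simple.
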